**CONSORT flow diagram of patient randomization.**

### Sample size calculation

To calculate the minimum sample size, we considered two possible comparisons: flossing vs. SDF/infiltration and SDF vs. infiltration. This approach follows since differences between SDF and infiltrant are expected to be lower and thus a bigger sample may be required to present statistical power. As no study has tested the SDF on approximal initial caries, we used differences between other tested treatments and/or similar treatments on other surfaces to estimate minimum expected difference among the groups tested in our protocol.

Considering flossing vs. other interventions, we considered a minimum difference of 30% [13], an alpha error of 5%, and a study power of 80%. A minimum sample size of 36 surfaces per group were found. To compare SDF and infiltrant, we considered 20% as minimum expected difference [9]. Then, the minimum sample size found was 86 surfaces. Rates considered for estimating differences among treatments were obtained from previous studies in permanent teeth. As caries progression tends to be faster in primary teeth [17], we believe similar or even smaller samples could achieve statistical power to prove existent differences in these teeth.

Considering we will include similar sample sizes for all groups, we assumed the biggest sample as reference (n = 258 surfaces). To ensure the power of the study, we added 30% to this sample to compensate possible follow-up drop-outs, totalizing a minimum sample size of 336 surfaces (112 surfaces/per group). Since child and adolescent patient characteristics were significantly different, we opted to conduct two parallel studies, with similar designs, each one including one of these groups of patients.

To compensate the clustering effect, since more than one surface may be included in each child/adolescent, we added an additional 50% on the calculation. Thus, we reached a final simple size of 504 surfaces (on average, 168 surfaces per group) to be included in this study.

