### Statistical analysis

The intra- and interexaminer reproducibilities in direct visual inspection and radiographic examination will be calculated by the unweighted and weighted Kappa test, depending on the evaluated outcome.

Univariate and multiple multilevel analyses will be used: i) to verify if the used treatment influences on efficacy and cost-efficacy for arresting initial caries lesions and ii) to test the association between different independent variables and treatment efficacy. Caries progression to evident cavities will be the main outcome considered in these cases. If necessary, surrogate outcomes will be used in these analyses. The relative risks and hazard ratios with 95% confidence interval (CI) will be calculated, respectively, after 2-year follow-up and considering all follow-up times. For all multilevel analyses, the surface, the tooth, and the child will be used as levels.

The following independent variables will be tested according to the level: i) surface: visible and disclosed biofilm on the approximal surface; ii) tooth: side; arch [35]; iii) child: age in years; number of daily toothbrushings; who toothbrushes; type of toothpaste; use of dental floss; who flosses; previous visit to a dentist; previous professional topical fluoride application; caries experience (dmfs + DMFS); simplified oral hygiene index [33]; number of active caries lesions in smooth surfaces; individual caries risk; and socioeconomic, behavioral, and dietary factors.

Poisson analysis will be used to assess the association between intervention and patient discomfort and parents’/adolescents’ satisfaction. The prevalence ratio or rate ratio with a 95% CI will be calculated, depending on the outcome considered. If necessary, relevant independent variables will be included for adjustment in the final models.

Interim-analyses will be performed on the primary outcome when 50% have completed 12-month and 24-month follow-up and also, when 100% of patients completed the 12-month follow-up.

The significance level for all analysis will be *P* < 0.05. For all multiples models tested, a level of significance of 0.20 will be considered for the variable entering into the model and a level of 0.05 for remaining in the model.

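### The plan does not say whether the 2-year relative risk or the all-visits hazard ratio, or the univariate or the multiple model, decides efficacy; all are read at P < 0.05

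*Protocol article*

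**What the plan says.** All of this stands in the Statistical analysis section of the protocol article unless noted.

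- **Models.** The treatment question is given to two kinds of model: "Univariate and multiple multilevel analyses will be used: i) to verify if the used treatment influences on efficacy and cost-efficacy".
- **Outcome.** "Caries progression to evident cavities will be the main outcome considered in these cases". The Primary outcome section names the same endpoint and attaches neither a time point nor an effect measure to it.
- **Effect measures.** "The relative risks and hazard ratios with 95% confidence interval (CI) will be calculated, respectively, after 2-year follow-up and considering all follow-up times". Under Follow-up examinations, the visual examinations that could feed the hazard ratio are at 6, 12 and 24 months.
- **Covariates of the multiple models.** "a level of significance of 0.20 will be considered for the variable entering into the model and a level of 0.05 for remaining"; this applies to a long list of surface, tooth and child variables.
- **Threshold.** "The significance level for all analysis will be" P < 0.05, without division.

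The Abstract says only that multilevel analyses will be used. The Sample size calculation works from differences in rates, with "an alpha error of 5%, and a study power of 80" percent. That hints at a proportion, but it gives no time point and names no deciding analysis.

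**The concern.** Taken literally, one pair of arms at the final analysis yields 2 measures × 2 models = 4 treatment results on the same outcome, each held to the full 5%.

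They are not the same question asked four times. The relative risk describes status at 2 years. The hazard ratio also uses the timing of progression and the partial follow-up of children lost before 24 months. The multiple models condition on covariates picked by their P-values. The results can therefore fall on different sides of 0.05, and the plan gives no rule for that case. The reader of the trial report could not tell whether the result presented as the efficacy finding was fixed beforehand, and the error rate of that finding would not be 5%.

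This is separate from the number of arm pairs, the interim analyses and the possible use of surrogate outcomes. It would remain if those were settled.

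**Working it through.** **Size of one comparison.** The plan's chain reproduces: 86 × 3 = 258; 258 × 1.3 = 335.4, given as 336; 336 × 1.5 = 504; 504 / 3 = 168 surfaces per group. With 141 participants per sub-study (Participant selection), that is 141 / 3 = 47 per arm and 504 / 141 ≈ 3.6 surfaces each. The 30% allowance covers a loss of 1 − 258/336 = 23%.

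**Ceiling.** If the tests were independent, the chance of at least one false positive would be 1 − 0.95² = 9.75% for two and 1 − 0.95⁴ = 18.5% for four. They share the same data, so the true figure is lower and has to be simulated.

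**Simulation under no treatment effect.** One pair of arms, one final look, 47 v 47 children, 1 + Poisson(2.57) surfaces each, visits at 6, 12 and 24 months, two-sided 5%, 1,500 trials per scenario. The relative risk came from a log-link Poisson model and the hazard ratio from a discrete-time complementary log-log model, both with standard errors robust to clustering by child. The multiple models used entry at 0.20 and retention at 0.05, with treatment forced in. The documents give no progression rates, cluster variance or covariate effects, so these are assumptions:

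- **A:** about 36% progression at 24 months, child frailty SD 0.7, 14 candidate covariates of which 3 prognostic, loss of 23% or 30%.
- **B1, B2, B3:** 12 candidates of which 3 prognostic, about 23% leaving early. B1: 15% progression, child SD 0.8, covariate effect 0.35. B2: 30%, 0.8, 0.35. B3: 30%, 0.4, 0.6.

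| Scenario | RR univ. | RR multiple | HR univ. | HR multiple | RR or HR, univ. | Any of four |
|---|---|---|---|---|---|---|
| A, 23% loss | 0.052 | 0.084 | 0.055 | 0.076 | 0.066–0.077 (both losses) | 0.124 |
| A, 30% loss | – | – | – | – | as above | 0.141 |
| B1 | 0.052 | 0.087 | 0.053 | 0.087 | 0.060 | 0.117 |
| B2 | 0.051 | 0.074 | 0.048 | 0.071 | 0.057 | 0.107 |
| B3 | 0.053 | 0.062 | 0.061 | 0.060 | 0.067 | 0.129 |

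The simulation error is √(p(1 − p)/1500), about 0.006 at p = 0.05 and 0.009 at p = 0.14.

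**How much of the excess is choice among versions.** Compare the excess over 5% in any of four with the excess already present in the multiple-model relative risk alone:

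- A, 23% loss: 3.4 of 7.4 points (46%).
- B1: 3.7 of 6.7 (55%).
- B2: 2.4 of 5.7 (42%).
- B3: 1.2 of 7.9 (15%).

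This split is rough. It shows that between about one seventh and one half of the excess sits in a single stepwise test, through covariate selection and robust errors with few clusters. Relative risk versus hazard ratio, univariate only, adds 0.7 to 2.7 points to 5%.

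**With a real effect.** Under set A's assumptions (single-test power about 60–74%), the univariate relative risk and hazard ratio disagreed on significance in about 11% of trials, and the four versions did not all agree in 25–27%. These figures come from that one set of assumptions and were not repeated under the others.

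**The case against.** **This belongs in an analysis plan.** Which measure and model is primary is often settled there, and none is shown. A mere omission would be no finding. But the article is not silent: it assigns two model types and two effect measures to one outcome and holds all of them to the same threshold. That fixes the analysis badly, so the point stands.

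**The count of four is one reading.** Entry and retention levels fit the common practice in which univariate runs only screen variables and the multiple model is final. That is a fair reading, and two versions then remain. The text nevertheless gives the univariate analyses to the treatment question as well, and on either reading the relative risk and hazard ratio are unranked.

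**A reader might infer that the plan lets any version crossing 0.05 establish efficacy.** It does not say so. It says that estimates with confidence intervals will be calculated. What can be said is that nothing rules such a choice out.

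**A reader might also attribute the whole 11–14% to choice among versions.** The split above does not support that. The simulations also use marginal models with child clusters and child-level covariates, whereas the plan has three levels and includes surface and tooth variables. The figures are indicative.

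**A reader might infer that the declared efficacy result drives the cost-efficacy model.** Second outcome measurements bases that model on the efficacy and cost data collected, not on which test is called positive, so this consequence is not supported.

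**Conclusion.** The concern holds in a limited form. For one pair of arms and one outcome at the final analysis, the article sets out several full-alpha results and does not say which decides.

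The part due to relative risk versus hazard ratio is small: about 6–8% instead of 5%, from the univariate pair. If univariate and stepwise multiple versions of both all count, the figure is roughly 11–14%, well short of a fourfold error because the tests are strongly correlated. Part of that belongs to the stepwise selection and to the robust errors used in the simulations. If univariate runs are only screening, the relevant pair is the two multiple models; their joint error was not computed, but each alone ran at 6–9%.

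All these sizes rest on assumed progression, clustering, covariate strength and drop-out. That no deciding analysis is named rests on the text alone.

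**What to change.** Add one statement to the Statistical analysis section: a single analysis decides efficacy for each comparison of arms. For example, this could be the relative risk of progression to an evident cavity at 2 years, from the multilevel model with treatment and a pre-specified list of baseline covariates. The hazard ratio over all visits could be named instead, provided only one is named.

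For that deciding model, the fixed list replaces selection at 0.20 and 0.05. Selection can stay for the plan's other aim, the association of the independent variables with treatment efficacy. Report the other effect measure and the other univariate and multiple models as supportive, with 95% confidence intervals and no significance claim.

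The change needs no extra patients or data. Trial status says recruitment is still under way, but the choice must be made without sight of outcome results by arm. The cost is that a result significant only in a supportive version cannot be called a positive efficacy finding.

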#### Inclusion criteria

Presence of at least one active initial caries lesion (scores 1, 2, or 3 according to International Caries Detection and Assessment System – ICDAS), detected by visual and tactile examination [18, 19] on approximal surfaces of primary molars for children or permanent premolar/molar for adolescents. For this purpose, surfaces will be evaluated after orthodontic rubber placement for at least 48 hours [20, 21], cleaned with dental flossing and clinically assessed by one trained and blinded examiner ([name]) after rubber removal. The approximal surfaces of interest for the study will be those that presented full contact with the adjacent tooth. All the surfaces eligible for this study will be included.

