#### Exclusion criteria

i) Presence of advanced dentine caries lesions detected by bitewing radiographic examinations (radiographic scores 4, 5, or 6) [15]. Only the surfaces presenting this condition will be excluded. The other eligible surfaces in the same patient will be maintained in the sample. ii) Children or adolescents that refuse to participate in the study or present negative behaviors.

Children that presented other needs for dental treatment will be referred to treatment in our Dental School. Moreover, all individuals will receive orientation about dietary and hygiene habits.

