### Random allocation

The three parallel groups of interventions are defined as SDF, caries resin infiltration, and control group (exclusively flossing instructions).

The individuals will be randomly allocated to each group according to a sequence obtained in appropriate statistical software (Medcalc software version 12.4.0.0, Ostend, Belgium). The generated sequence will be distributed in opaque and sealed envelopes, which will be opened by the operators ([name]) only at the moment of the interventions.

All individuals enrolled in the study will receive in each included surface the active intervention, the placebo therapy, and instruction for daily flossing this specific surface. When the active treatment is exclusively flossing, two placebo therapies will be used, as described below. All procedures will be performed sequentially in a same surface by trained operators ([name]), in the same appointment.

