### Primary outcome

A single trained, calibrated, and blinded examiner ([name]) will assess caries lesions progression by direct visual exam using ICDAS and an adjunct index to assess caries lesion activity status [23]. The ICDAS score and the activity status will be assessed after tooth separation for at least 48 hours. The main outcome considered will be caries progression to evident dentine cavitated caries lesion. Bitewing radiographs will be taken to evaluate possible caries progression into dentin according to Ekstrand et al. [15]. The progression detected by radiographs or by ICDAS scores transition, as well as changes in the caries lesion activity status, will be considered as possible surrogate outcomes.

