### Follow-up examinations

At baseline, independent variables will be collected for each patient. In addition, for each included surface, the ICDAS and radiographic scores will be registered, as well as the caries activity status.Patients will be assessed after 1, 3, 6, 12, and 24 months. At the 1- and 3-month follow-up the independent variables related to presence of biofilm will be re-evaluated. At other follow-ups (6, 12, and 24 months), direct visual examination of enrolled surfaces will be performed after tooth separation for 48 hours. Moreover, radiographic examination will be performed on the 12- and 24-month follow-up visits (Figure 2). The examinations will be performed as explained in previous sessions.

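### The covariate list for the caries models leaves out baseline ICDAS and radiographic score of the treated surface, although both are recorded: a cheap chance to correct for chance imbalance and gain power is missed

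*Protocol article*

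**What the plan says.** Under Statistical analysis, univariate and multiple multilevel models serve two aims: to see whether treatment affects efficacy, and to test associations between other variables and efficacy. Relative risks at two years and hazard ratios over all visits are reported. The variables to be tested are then listed by level. The surface and tooth entries are "surface: visible and disclosed biofilm on the approximal surface; ii) tooth: side; arch". The child-level list is long (age, brushing, flossing, fluoride, caries experience, caries risk and others). One selection rule governs every multiple model: "a level of significance of 0.20 will be considered for the variable entering into the model and a level of 0.05 for remaining".

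Under Follow-up examinations, at baseline "for each included surface, the ICDAS and radiographic scores will be registered, as well as the caries activity status".

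Entry allows a spread of severity. The inclusion criterion is "Presence of at least one active initial caries lesion (scores 1, 2, or 3 according to International Caries Detection and Assessment System"), and surfaces are excluded for "Presence of advanced dentine caries lesions detected by bitewing radiographic examinations (radiographic scores 4, 5, or 6"), so radiographic scores below 4 remain. Under Primary outcome, "The main outcome considered will be caries progression to evident dentine cavitated caries lesion".

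Under Random allocation, "The individuals will be randomly allocated to each group according to a sequence obtained in appropriate statistical software". No stratification by lesion severity is described.

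**The concern.** ICDAS and radiographic score are the scales on which progression is judged. A surface that enters at ICDAS 3 is nearer to cavitation than one that enters at ICDAS 1, so the starting score is a natural prognostic variable for the primary outcome. It is also natural for the surrogate outcomes, which are changes on the same scales. The plan collects both scores and then names neither among its covariates.

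Nothing else in the list stands in for them. Caries experience, individual caries risk and the number of active smooth-surface lesions describe the child; they cannot separate an ICDAS 1 surface from an ICDAS 3 surface in the same mouth. The Independent variables section does not name the two scores either. The sentence that allows further relevant variables for adjustment belongs to the Poisson analysis of discomfort and satisfaction, not to the caries models.

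At stake are the efficiency of the primary comparisons and their protection against an unlucky allocation. If severity were added only after an imbalance had been seen, the adjustment would also be driven by the data.

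**Working it through.** **The plan's own figures.** 86 × 3 = 258 surfaces; 258 × 1.30 = 335.4, taken as 336; 336 × 1.5 = 504, or 168 per group. The chain reproduces, and the point does not depend on it. Participant selection gives 141 individuals per cohort, so 141 / 3 = 47 per arm if all are randomised, and 504 / 141 = 3.57 surfaces each if the 504 applies to each cohort, as the Abstract says.

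**What the document does not give.** It has no severity mix at entry, no progression risk by baseline score and no within-child correlation. All values below for these are assumptions.

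**1. Simple calculation.** Assume independent surfaces and half the lesions at ICDAS 3. The SE of the between-arm difference in that share is √(2 × 0.25 / n).
- n = 86: SE 0.0762; a difference of at least 10 points in either direction has probability 0.19.
- n = 112: SE 0.0668; probability 0.13.

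Assume 24-month cavitation of 40% for ICDAS 3 and 10% for ICDAS 1–2. A 10-point imbalance then moves the risk difference by 0.10 × (0.40 − 0.10) = 3 points. The mean risk is 25%, so the SE of the risk difference at n = 86 is √(2 × 0.25 × 0.75 / 86) = 6.6 points. The shift is 3 / 6.6 = 0.45 of one SE.

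The share of outcome variance explained by severity is 0.15² / (0.25 × 0.75) = 12%, or 0.10² / (0.15 × 0.85) = 7.8% if the risks are 25% and 5%. The gain in effective sample is 1 / (1 − R²) = 1.14 or 1.09. In interval width, 1 − √(1 − R²) = 6% or 4%. These formulas apply to a risk difference.

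**2. Simulation with clustering of severity.** Two arms of 47 individuals, about 3.6 surfaces each, 40% deeper lesions, no treatment effect. The crude risk difference was compared with one stratified by baseline depth. Entries are the variance of crude over adjusted, by within-child correlation (ICC) of depth.

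| Risk, shallow / deep | ICC 0.05 | ICC 0.20 | ICC 0.40 | Shift per 10-point imbalance |
|---|---|---|---|---|
| 0.15 / 0.30 | 1.02 | 1.05 | 1.06 | 1.5 points |
| 0.10 / 0.40 | 1.17 | 1.25 | 1.33 | 3 points |
| 0.10 / 0.60 | 1.46 | 1.62 | 1.91 | 5 points |

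An imbalance of at least 10 points arose in about 8% to 22% of allocations. The crude estimate averaged about zero throughout, so there was no systematic bias. Outcomes within a child were taken as independent given depth; further within-child correlation would add to both variances and bring the ratios nearer to 1.

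**3. The planned effect measures.** With 40% / 10% risks, 86 independent surfaces per arm, visits at 6, 12 and 24 months and no treatment effect, the median SE of the log hazard ratio was 0.307 unadjusted and 0.308 adjusted. For the log relative risk it was 0.267 and 0.251, about 6% smaller. A rerun of this simulation gave the same picture. For the hazard ratio the interval therefore does not narrow. The gain is in power: when treatment works, leaving out a strong predictor pulls the hazard ratio towards 1 while the SE hardly changes.

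**The case against.** Four points can be made for the plan.

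- **The list may not be the adjustment set.** It can be read as the candidate set for the second aim, the study of associations, and a fuller document might fix the covariates of the primary model. This stands in part. But the article enumerates its variables level by level and applies the selection rule to all multiple models, and nothing in it brings baseline severity in. The absence of stratification is weaker evidence, because a condensed article may simply not mention it.
- **Randomisation already deals with imbalance.** This stands. A reader might infer that the treatment effect will be biased, or that its confidence interval is invalid. The document does not support that: the unadjusted contrast is unbiased on average, and its interval already allows for chance imbalance. In the simple calculation the 3-point shift is under half an SE. Setting it against the 20-point target difference would make it look more serious than it is.
- **The precision gain is assumed and tied to the scale.** This stands. A reader might infer that all the planned intervals are wider than necessary. That holds in some degree for the risk difference and relative risk, but not for the hazard ratio.
- **Adjustment has a price.** Under the assumed mean risks of 15% and 25%, 86 surfaces give 86 × 0.15 = 12.9 to 86 × 0.25 = 21.5 events per arm. Two categorical and probably correlated scores in a three-level model could strain that. This is a reason for sparing coding, not for omission.

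**Conclusion.** The omission is real and worth correcting, as an improvement at almost no cost rather than the repair of an invalid analysis. The article records two baseline measures on the outcome's own scales, admits surfaces that differ on both, and names neither in its covariate list. The unadjusted comparison remains valid. What is lost is the correction of chance imbalance in severity, and some power or precision.

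The size cannot be fixed from the document. Under the assumed rates, the variance of the unadjusted risk difference ranges from 1.02 times the adjusted one (negligible) to 1.9 times (substantial), and from 1.17 to 1.33 at 10% versus 40% progression. That severity predicts cavitation follows from the nature of the scales; that it is the strongest predictor the trial holds is not shown. Baseline activity status is also unlisted, but it should hardly vary, because only active lesions qualify.

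**What to change.** In the Statistical analysis section:

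1. Add baseline ICDAS score and baseline radiographic score to the surface-level variables.
2. Pre-specify both, with treatment, in the primary efficacy models, coded sparingly (for example as ordinal scores) in view of the limited number of events.
3. State that treatment and these two terms are exempt from the 0.20 entry and 0.05 retention rule. Listing the scores without this would let the rule drop them.
4. Keep the unadjusted analysis as a sensitivity analysis.
5. State that the adjusted relative risk and hazard ratio are conditional on baseline severity.

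The cost is a few sentences, a few more model parameters and a slightly different, conditional estimand. The data are already planned for collection and no stated sample size changes. The change should be made before outcome data are examined, including at the planned interim analyses.

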## Discussion

This trial aims to propose a possible efficacious treatment for initial caries lesion on approximal surfaces, which could be useful in private and public contexts representing an easier and effective option to treatment of enamel approximal caries in children and adolescents.

In theory, it is known that initial caries lesions could be arrested by biofilm removal [36]. In fact, dental flossing would be the simplest procedure for biofilm removal to control initial lesions on approximal surfaces. However, this control depends on correct and frequent flossing by patients [3], which could explain the difficulty in arresting lesions in these specifics areas [6]. When flossing is not effective, it is necessary to resort to other possibilities to control caries lesions. That is why it is important to evaluate flossing comparatively to other available options in order to seek for the simplest and most cost-efficacious/effective treatment.

Previous studies evaluated the preventive effect of SDF [22] and/or its efficacy on dentine lesions [7, 37]. However, few studies assessed its efficacy on initial caries lesion [8, 9]. In addition, no previous study verified its application on approximal surfaces. A systematic review showed that SDF seems to be more effective than fluoride varnish [38]. A possible explanation for this superior effect could be the fluoride concentration on SDF, which is higher than that found in the fluoride varnish [39]. However, the effect of SDF on caries lesions could be explained not only by fluoride action, but also by the silver ions, which react with thiol groups in amino and nucleic acids leading to bacterial lysis [38], and thus to probable quicker caries arrestment [8, 40], especially if compared to other options of arresting initial caries lesions such as other fluorides.

There are some aesthetic concerns regarding the use of SDF since it could cause black staining on carious lesions due to the precipitation of silver [38]. However, aesthetics did not seem to be jeopardized in the case of initial caries lesions on approximal surfaces of posterior teeth due to their localization. However, the staining could be a limitation of our study regarding examiners’ blinding, since it could suggest which surfaces were treated with SDF. Nevertheless, inactive lesions could also present dark coloring, minimizing this limitation [8, 22].

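### The 0.20/0.05 selection rule covers every multiple model without exempting treatment, and biofilm and floss-use covariates are not limited to baseline values

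*Protocol article*

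**What the plan says.** The Statistical analysis section gives the univariate and multiple multilevel analyses two purposes. The first is "to verify if the used treatment influences on efficacy and cost-efficacy for arresting initial caries lesions"; the second is "to test the association between different independent variables and treatment efficacy". Relative risks and hazard ratios with 95% confidence intervals are promised.

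The section closes with one rule for both purposes, applied to every multiple model: "a level of significance of 0.20 will be considered for the variable entering into the model and a level of 0.05 for remaining in". It states no exception for treatment group.

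The surface-level candidates are "visible and disclosed biofilm on the approximal surface". Use of dental floss is a child-level candidate. Neither has a measurement time. The Follow-up examinations section has independent variables collected at baseline and adds: "At the 1- and 3-month follow-up the independent variables related to presence of biofilm will be re-evaluated". The Abstract confirms that these two visits come after treatment.

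**The concern.** Treatment group is the randomised exposure. Its estimate and interval should be reported whatever its P value, above all where a small difference is an informative result. The Sample size calculation section expects SDF and infiltration to differ less than either differs from flossing. If treatment must reach P<0.05 to stay in the model, a non-significant adjusted contrast disappears, and those that remain are too large on average.

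The second issue is timing. A covariate measured after allocation can be a consequence of treatment. The Discussion explains SDF's effect partly by silver ions "which react with thiol groups in amino and nucleic acids leading to bacterial lysis", so later biofilm could lie on the causal path. Adjusting for it would then remove part of the effect under study and weaken the protection that randomisation gives.

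**Working it through.** **1. The plan's own figures.** The Sample size calculation section gives alpha 5%, power 80%, differences of 30% (36 surfaces per group) and 20% (86 surfaces), but no rates. I assume a two-sided test and use n = [1.960·√(2p̄q̄) + 0.842·√(p₁q₁ + p₂q₂)]² / d².
- 15% vs 45%: (1.270 + 0.515)² / 0.09 = 35.4, so 36.
- 23% vs 43%: (1.303 + 0.547)² / 0.04 = 85.6, so 86.
- 86 × 3 = 258; 258 × 1.3 = 335.4, taken as 336; 336 × 1.5 = 504, or 168 per group.

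The figures reproduce, given those unreported rates. Each arm is thus sized for 80% power on SDF versus infiltration.

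**2. Effect of a P<0.05 retention filter on one treatment contrast.** Let δ be the expected Z. I assume that entry and retention are judged on the same statistic, so the 0.05 limit is the binding one. Retention probability is Φ(δ − 1.96). Average inflation among retained estimates is [δ + φ(δ − 1.96)/Φ(δ − 1.96)] / δ.

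| Contrast | δ | Retained | Dropped | Inflation if retained |
|---|---|---|---|---|
| SDF vs infiltration, 80% power | 1.960 + 0.842 = 2.802 | 80% | 20% | (2.802 + 0.280/0.80)/2.802 = 1.125 |
| Same, if power were only 50% (assumed) | 1.960 | 50% | 50% | (1.960 + 0.399/0.50)/1.960 = 1.407 |
| Flossing vs active treatment | 2.80 × √(86/36) = 4.33 | Φ(2.37) = 99% | 1% | (4.33 + 0.0241/0.991)/4.33 = 1.006 |

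A simulation with 2,000,000 draws gave 1.125 at 80% power and 1.408 at 50%. The last row assumes that the drop-out and clustering allowances suffice.

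**3. Effect of adjusting for post-treatment biofilm.** The documents give no mediated share, so this is illustration only. If a share s of the log relative risk runs through biofilm, the adjusted RR is about RR^(1−s). With an assumed total RR of 0.50:
- s = 0: 0.50.
- s = 0.25: 0.50^0.75 = 0.59.
- s = 0.50: 0.50^0.50 = 0.71.

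A simulation (assumed: 86 per arm, progression 40% vs 20%, biofilm RR 2.5, no clustering) gave adjusted RRs of 0.50, 0.59 and 0.70. Treatment kept P<0.05 in 85%, 56% and 24% of repeats, against 81–82% unadjusted.

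**4. Covariate selection with treatment forced in.** A simulation with 47 per arm, 20 noise covariates and 1,500 repeats gave a type I error of 0.055. Its Monte Carlo standard error is √(0.055 × 0.945/1500) = 0.006, so this is compatible with 5%. Covariate selection as such does little harm here; the problem would come from filtering treatment or from using post-treatment values.

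**The case against.** A reader might infer that the plan deliberately puts treatment through the selection rule, so that the trial's main result appears only when significant. The documents do not support that. Treatment is not named among the candidate variables. The paragraph on Poisson analysis treats intervention as the exposure and the independent variables as adjusters, which suggests that the rule was meant for covariates. The rule concerns multiple models only, so an unfiltered univariate treatment estimate remains, and nothing makes the adjusted estimate the main one.

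A reader might also infer that post-treatment biofilm will be adjusted for. That is not stated either. Independent variables are collected at baseline, and use of baseline values alone is an open reading. The Discussion links bacterial lysis to lesion arrest; it does not say that SDF lowers visible biofilm 1 to 3 months later. It also expects daily flossing not to be influenced by the intervention received. The mediated share may be zero.

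Finally, the 20% and 12% figures do not apply to treatment in general. They fit SDF versus infiltration. Treatment has three arms, and the plan does not say whether it would be retained jointly or by contrast.

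All of this stands and limits the point. It does not remove it: the sentence covers all multiple models, those models include the ones that test treatment, and no sentence settles which biofilm or flossing measurement enters.

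**Conclusion.** The point holds as two gaps in a rule that the protocol itself fixes: treatment is not exempted from selection, and two candidates that can change after treatment are not tied to baseline.

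On a literal reading, the adjusted SDF versus infiltration estimate would be dropped in about 20% of repeats at 80% power, with about 12% average inflation when retained. For flossing versus active treatment the figures are about 1% and 0.6%. These rest on a two-sided 5% test, a normal approximation, retention judged contrast by contrast, and adequate drop-out and clustering allowances. The attenuation from post-treatment biofilm cannot be sized from the documents.

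Neither gap shows that the trial's main comparison is biased. Both leave to the analyst a choice that should be closed before results are seen, and interim analyses of the primary outcome are planned.

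**What to change.** In the Statistical analysis section, state that:
- treatment group stays in every model whatever its P value;
- efficacy models adjust only for prespecified variables measured at baseline, including biofilm and floss use if wanted;
- the 0.20/0.05 selection serves only the exploratory risk-factor aim, with treatment forced in;
- biofilm at 1 and 3 months is analysed as a separate outcome.

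The first statement and the restriction to baseline close the two gaps. Prespecifying the adjustment list adds clarity, but the type I error check does not show it to be essential. The cost is wording and a slightly less parsimonious efficacy model; trial conduct does not change.
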